## 3. Background and rationale

Adolescent pregnancy remains a significant public health concern worldwide, including in Thailand. According to the United Nations Sustainable Development Goals (SDGs) progress report, the global adolescent birth rate showed a slight decline, from 45 per 1,000 live births in

2015 to 44 in 2019 (United Nations, 2019). In the United States, the birth rate among females aged 15–19 years decreased from 17.4 per 1,000 in 2018 to 16.7 in 2019 (Martin, Hamilton, & Osterman, 2021). In Thailand, data from 2015 to 2019 indicate a consistent decline in adolescent births among females aged 15–19 years, with rates of 44.8, 42.5, 39.6, 35.0, and 31.3 per 1,000, respectively (Thailand Ministry of Public Health, 2020). Despite this downward trend, the rate remains above the target set by the SDGs, which aim to reduce adolescent birth rates among individuals aged 10–19 years by 2030. Furthermore, Thailand’s National Strategy on Adolescent Pregnancy Prevention and Resolution (2017–2026) has established a national goal to reduce the birth rate among females aged 15–19 years to no more than 25 per 1,000 by 2026 (Thailand Ministry of Public Health, 2017).

Adolescent pregnancy remains stubbornly high, falling short of global and national reduction goals and hampering both maternal-child health and wider social and economic progress. Young mothers must cope with rapid physical, psychological, and social changes while taking on the responsibilities of parenthood, a transition often clouded by fear and anxiety about raising a child (Mangeli et al., 2017). Because they are still developing themselves, they may lack the knowledge, experience, and emotional maturity needed for confident caregiving, especially in the early postpartum period (Ngai & Chan, 2012). These challenges can undermine their sense of parenting efficacy and limit the quality of care they can provide.

Parental stress is the tension caregivers feel when child-rearing demands seem to outstrip their available resources. For adolescent mothers, who are still navigating their own development, the early postpartum period is especially sensitive. During these weeks, they must learn basic caregiving skills, bond with their infants, and decipher newborn cues. If they believe they are falling short of their own or others’ expectations, anxiety can hinder their adjustment to the maternal role. To ease this stress, young mothers often turn to trusted confidants, seek guidance while still in the hospital, consult more experienced peers, or look for information online (Yodthong, Usaha, & Poopatayakon, 2020).

Parental competence refers to a mother’s positive attitudes, practical knowledge, and caregiving skills, qualities that allow her to handle child-rearing tasks well and find satisfaction in motherhood. Many adolescent mothers struggle to develop this competence, however. The added responsibilities of parenting collide with their own ongoing physical and emotional changes, often leading to stress, anxiety, ineffective caregiving, and role conflict (Mangeli et al., 2017). Together, these pressures can undermine their confidence and caregiving ability, highlighting the need for age-appropriate, targeted interventions that build their parenting skills.

Effective support for adolescent mothers requires nurses to cultivate a positive attitude and maintain open communication, thereby facilitating an accurate understanding of each mother's needs. Such rapport can alleviate maternal anxiety and foster adaptation to the maternal role (Erfina et al., 2019; Intrakasem et al., 2019). Care should emphasise role adjustment through education, hands-on skill-building in infant care and breastfeeding, and structured activities that strengthen the mother–infant bond, all of which promote maternal confidence. Because adolescents are frequent users of digital technology, integrating social media and other online platforms into postpartum care represents an essential component of contemporary service models (Mekkamon & Wichienprapha, 2018). Current postpartum practice, however, often falls short of these ideals. Routine hospital discharge within 2–3 days limits opportunities for comprehensive and continuous skill development, and most institutions provide no structured follow-up or communication system after discharge, relying instead on printed manuals for self-study. This discontinuity may heighten anxiety and undermine caregiving effectiveness once mothers return home.

A review of the literature, corroborated by the researcher's clinical experience, indicates that postpartum care for adolescent mothers remains largely indistinguishable from that offered to adult mothers. Instruction is typically delivered through lectures, demonstrations, and brief skills training sessions. Yet adolescent mothers are seldom provided with accessible, engaging resources for later review: most information is still distributed as manuals, pamphlets, or compact discs, formats that neither match adolescents' media preferences nor sustain their attention. Opportunities for convenient follow-up consultation are likewise scarce. Accordingly, this study seeks to design and evaluate a technology-enhanced care model tailored to the specific needs of adolescent mothers.

The LINE application is currently one of the most widely used communication platforms in Thailand. A 2020 survey reported approximately 47 million LINE users nationwide, with members of Generation Z spending an average of 12 hours 8 minutes online each day (Thailand Electronic Transactions Development Agency, 2020). Owing to its popularity and accessibility, LINE offers a promising channel for engaging adolescents. The LINE Official Account enables large-scale dissemination of text, images, videos, and announcements, while also permitting followers to send private messages for confidential consultation; these interactions are invisible to other users and incur no costs beyond routine internet connectivity. Consequently, leveraging a LINE OA for health-education delivery could strengthen communication and furnish adolescent mothers with a convenient, private avenue for obtaining advice and support from healthcare professionals.

The research team developed a Parental Enhancing Program with Line Official Account “Parent Paplearn”. The platform delivers evidence-based content on infant cues and appropriate caregiver responses, newborn care, breastfeeding, infant bathing, and the early recognition of neonatal abnormalities. Materials are presented in multiple formats, infographics, e-books, and short videos, allowing adolescent mothers to review information and seek consultation at their convenience. By combining on-demand educational resources with a confidential communication channel, the program is designed to strengthen parenting competence and mitigate parenting stress among adolescent mothers. Findings from the evaluation of this intervention are expected to inform refinements to postpartum-care systems and to advance support for adolescent mothers in fulfilling their caregiving responsibilities effectively.

#### **4. Review literature**

The researcher reviewed relevant literature and studies as follows:

##### **1. Adolescent Pregnancy**

Adolescent pregnancy refers to pregnancy in females aged 10–19 years, measured at the time of childbirth. It can be further categorized into adolescent pregnancy (ages 15–19) and younger adolescent pregnancy (ages 10–14).

##### **Impacts of Adolescent Pregnancy**

1. **Physical** Adolescents’ bodies are still developing, which may increase health risks compared to adults. Most adolescent pregnancies are unplanned, potentially leading to inadequate prenatal care and behaviors, resulting in complications such as anemia, insufficient weight gain during pregnancy, pregnancy-induced hypertension, difficult labor, preterm birth, postpartum hemorrhage, low birth weight, miscarriage, or neonatal death (Althabe et al., 2015; Ogawa et al., 2019).

2. **Psychological** Mental health issues are common among pregnant adolescents. They often experience shame, guilt over unintended pregnancy, and social or familial rejection, which can cause anxiety, stress, and may develop into depression (Corcoran, 2016; Osok et al., 2018).

3. **Family** Families of pregnant adolescents often face stress, anger, and disappointment. Social stigma associated with adolescent pregnancy adds further burden, increasing the caregiving responsibilities for both the adolescent mother and her child (Jareesri, 2018).

4. **Social and Economic** A significant social issue related to adolescent pregnancy is illegal abortion, which can lead to severe health complications such as hemorrhage and

infection. Additionally, inadequate child-rearing or abandonment may occur, resulting in societal challenges and lower quality future workforce. The government incurs costs for healthcare and social welfare related to adolescent pregnancy (Jareesri, 2018).

## **2. Concept of the Maternal Role**

### **2.1 Theory of Maternal Role**

Rubin (1975) developed the Theory of Maternal Identity, which involves the following processes:

Replication: Women mimic or model their maternal behavior after their own mothers or other maternal figures.

Fantasy: Women imagine how they will perform their maternal role and how they will care for their child in the future.

Dedifferentiation: Women learn the maternal role by seeking role models among close individuals, then choose a model that fits them or reject roles they find unsuitable.

Identity Formation: Women establish a maternal identity by adopting a role that suits them, accepting their new role, expressing satisfaction, and effectively fulfilling maternal responsibilities.

In 1985, Mercer expanded on Rubin's concept, describing maternal role development as a continuous and dynamic process from pregnancy through postpartum, consisting of four stages (Mercer, 2004):

1. **Commitment, Attachment, and Preparation** This stage occurs during pregnancy, where women prepare for motherhood by caring for their health, seeking information on pregnancy care, developing an attachment to the fetus, and learning about the maternal role.

2. **Acquaintance, Learning, and Physical Restoration** Starting from childbirth until six weeks postpartum, women begin to enact the maternal role according to advice and expectations from others.

3. **Moving Toward a New Normal** From two weeks to four months postpartum, mothers increasingly express their maternal role in a way that reflects their own characteristics, based on experience and learning.

4. **Achievement of Maternal Identity** After four months postpartum, mothers gain confidence, competence in child-rearing, and satisfaction in fulfilling their maternal role.

Successful maternal role attainment can be evaluated by three components: 1) attachment to child, 2) confidence/ competence in role, and 3) gratification/ satisfaction.

## **2.2 Parental stress**

Stress is a physiological and psychological response triggered by threatening stimuli (stressors), resulting in discomfort, anxiety, confusion, and imbalance.

Parental stress refers to the emotional reactions arising from various challenges encountered in child-rearing. Parenting is a new role that involves learning how to care for the child, building a parent-child relationship, and understanding the child's behavior. If adolescent mothers are unable to meet their own or others' expectations in caregiving, they may experience distress and anxiety. This can negatively affect their adjustment to the maternal role (Yodthong, Usaha, & Poopatayakon, 2020).

Abidin (1995) proposed that when parents are unable to effectively manage child-rearing tasks or respond appropriately to their child's needs in accordance with personal and societal expectations, they may experience a sense of failure in fulfilling their parental role, referred to as dysfunctional parenting. Based on this perspective, Abidin developed the Theoretical Model for the Parenting Stress Index (PSI), which explains the relationship between parental stress, parenting behavior, and child outcomes. The model comprises three core components:

- 1) **Parental Distress:** Refers to the emotional discomfort and psychological burden a parent experiences in fulfilling the caregiving role. It may stem from personal limitations, lack of support, or role dissatisfaction.

- 2) **Parent–Child Dysfunctional Interaction:** Represents the parent's perception that their child does not meet expectations and that interactions between the parent and child fail to generate a sense of satisfaction in the parental role. This often results in negative emotional experiences.

- 3) **Difficult Child:** Refers to the parent's perception of the child as temperamentally difficult or behaviorally challenging, making caregiving feel overwhelming and difficult to manage.

These components interact and contribute to overall parenting stress (Figure 1).

[figure not shown]

**Figure 1** The conceptual framework diagram of Parenting Stress Index

### 2.3 Parental competence

Parental competence refers to parents’ self-assessment of their ability to fulfill child-rearing responsibilities in accordance with personal or societal expectations. For instance, a mother may evaluate whether she is caring for her child effectively based on these standards (Vance & Brandon, 2017). Perceived parenting ability is closely associated with actual parental competence and reflects the overall quality of child-rearing.

#### Assessment of Parental Competence

Parental competence is assessed using the Parenting Sense of Competence Scale (PSOC), developed by Gibaud-Wallston and Wandersman (1978). The scale comprises two dimensions: 1) Efficacy: This dimension reflects the parents’ perception of their ability to fulfill parenting responsibilities and solve problems related to child-rearing. 2) Satisfaction: This emotional dimension captures feelings such as anxiety, pride, and a sense of accomplishment in parenting.

### 3. Factors Influencing competent parental functioning

Belsky’s “A Process Model of Competent Parental Functioning” (Belsky, 1984). to elucidate the various factors influencing parental roles in childcare. This model identifies three domains, including 1) ‘Personal psychological resources of parents’ domain encompasses individual characteristics. It has been found to exert the most significant influence on parental functioning. 2) ‘Contextual sources of stress and support’, which can either facilitate or hinder effective parenting, and 3) ‘Characteristics of the Child’, which may also influence parenting dynamics but generally have a lesser impact compared to the other two domains.

#### 1. Personal psychological resources of parents

1.1 **Age** reflects developmental stages, such as adolescence or adulthood, which indicate an individual’s readiness in physical, psychological, and social aspects. Adult mothers

tend to have better cognitive and problem-solving skills, which enhance their parenting competence (Shrooti et al., 2016).

**1.2 Marital Status** Single mothers bear the full responsibility of child-rearing, which may lead to increased stress and psychological challenges.

**1.3 Economic Status** Mothers with sufficient income tend to feel financially secure, enhancing their perceived parenting competence. In contrast, financial hardship can increase stress and lower parenting efficacy (Shrooti et al., 2016).

**1.4 Educational Level** Higher education improves information processing, problem-solving, and adaptability, contributing to more effective parenting (Shrooti et al., 2016).

**1.5 Parity** Previous childbearing experiences enhance maternal skills. Successful prior parenting experiences support more competent current parenting (Barabach et al., 2017).

**1.6 Physical Health** Chronic illness, complications, or medical conditions may require additional self-care, potentially reducing a mother's capacity to care for her child (Maehara et al., 2016).

**1.7 Pregnancy Readiness** Mothers who are prepared for pregnancy are more likely to engage in prenatal care and effective parenting (Shrooti et al., 2016).

**1.8 Self-Esteem** High self-esteem supports effective coping and adaptation, leading to improved parenting performance (Shrooti et al., 2016).

**1.9 Mental Health** Stress, anxiety, or depression may negatively affect parenting effectiveness (Angle et al., 2015; Shorey et al., 2015).

**1.10 Self-Efficacy** High maternal self-efficacy enhances confidence in parenting abilities, contributing to successful child-rearing practices.

## **2. Contextual sources of stress and support**

**2.1 Social Support** enhances maternal parenting competence through the provision of resources, information, and emotional encouragement in child-rearing (Brown et al., 2016).

**2.2 Marital Relationship** A positive and caring relationship with a spouse fosters maternal support and reinforces parenting abilities (Kershaw, 2014).

## **3. Characteristics of the Child**

**3.1 Child's Health Status** Infants with complications such as low birth weight, prematurity, or congenital disabilities may cause maternal stress, which can negatively affect parenting competence (Korja, Latva, & Lehtonen, 2012).

**3.2 Child's Temperament** Children who are difficult to soothe or prone to frequent crying may be perceived by mothers as challenging to manage, which can diminish maternal perceptions of parenting effectiveness and competence (Ponomartchouk & Bouchard, 2015).

#### **4. Line official account in Health Promotion**

The LINE Official Account is a feature of the LINE application designed for business or organizational use, allowing for the broader dissemination of information. It supports various multimedia formats, including text, images, posters, and videos, for convenient and effective communication with followers. Additionally, it enables two-way communication, allowing followers to send private messages for inquiries or consultations without other users seeing the exchange.

A key advantage of the LINE application is its ability to form group chats, where members, typically sharing similar experiences or characteristics, can communicate efficiently. A single message sent within the group reaches all members, enhancing group interaction. The application supports diverse file types (e.g., text, voice, images, videos, stickers, posters, and documents), enabling communication to be tailored to specific target audiences. Moreover, LINE reduces communication costs by allowing free voice calls through internet packages, eliminating the need for traditional phone charges (Kanabun, 2017).

Thailand, like the rest of the world, has entered the Digital 4.0 era, marked by the integration of intelligent technologies into various sectors, including healthcare. This transition has led to the rise of digital health platforms such as mobile applications, websites, electronic messaging, wearable devices, and health monitoring sensors, which aim to enhance the efficiency of healthcare services.

Among these tools, the LINE application has emerged as an effective communication platform, particularly well-suited to reaching adolescents. The LINE Official Account, designed for broad dissemination of information, allows for the easy sharing of messages, images, videos, and announcements with followers. It also enables private two-way communication, where followers can consult or inquire without their messages being visible to others.

As a free, internet-based communication channel, the LINE Official Account offers a private, accessible, and cost-effective means of interaction. Utilizing this platform to disseminate health information can improve communication between adolescent mothers and healthcare providers, offering a convenient and timely channel for consultation and support.

## 5. Objectives

1. Developed a Line Official Account “Parent Paplearn”.
2. To compare parenting stress among postpartum adolescent mothers who participated in the parental enhancing program with the mobile application through ‘Line Official Account™ Parent Paplearn’ and those receiving standard postpartum care.
3. To compare parenting competence among postpartum adolescent mothers who participated in the parental enhancing program with the mobile application through ‘Line Official Account™ Parent Paplearn’ and those receiving standard postpartum care.

## 6. Research framework

This study applies Belsky's “A Process Model of Competent Parental Functioning” (Belsky, 1984). to elucidate the various factors influencing parental roles in childcare. This model identifies three domains including 1) ‘Personal psychological resources of parents’ domain encompasses individual characteristics. It has been found to exert the most significant influence on parental functioning. 2) ‘Contextual sources of stress and support’, which can either facilitate or hinder effective parenting, and 3) ‘Characteristics of the Child’, which may also influence parenting dynamics but generally have a lesser impact compared to the other two domains.

The researchers utilized the parental competence framework to design the parental enhancing program with mobile application through ‘Line Official Account™ Parent Paplearn’. This program specifically targets contextual sources of stress and support, positioning nurses as vital resources to assist adolescent mothers in effectively caring for their children. In Thailand, nurses play a pivotal role in providing care through the nursing process, providing clients with appropriate education, and offering counselling. The program emphasizes the provision of knowledge and training in essential childcare skills, thereby enabling these mothers to perform their parenting roles with increased competence. Furthermore, it offers continuous support via mobile application through the ‘Line Official Account™ platform, facilitating timely responses to questions and concerns. This ongoing support not only alleviates parenting-related stress but also enhances the mothers' overall competence in childcare (Figure 2).

[figure not shown]

**Figure 2.** Research framework.

## 7. Research hypothesis

1. Participants in the intervention group experienced significantly lower levels of parental stress compared to those in the control group.
2. Participants in the intervention group experienced significantly higher scores in parental competence compared to those in the control group.

## 8. Keywords

Parental Program, Line Application, Parental Stress, Parental Competence, Adolescent Mothers

## 9. Research Design

This study employed a quasi-experimental control group pre-post-test design

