### 10.4 Inclusion criteria

1. Full-term deliveries (37-42 weeks)
2. Postpartum women aged 15 to 19
3. Mother without postpartum complications such as postpartum hemorrhage, preeclampsia with severe features, etc.
4. Infants exhibited no severe complications or congenital anomalies necessitating NICU admission or separation from the mother.
5. Mother intended to childcare for six-week
6. Participants could read, write, and communicate in Thai.
7. Demonstrated the ability to communicate via mobile using the LINE application.

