### 10.5 Informed consent process

The researcher explained the study objectives, procedures, and participants' rights. Informed consent forms were then obtained from the participants, with parental or spousal consent required for those under 18.

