### 10.6 Instrument

#### 10.6.1 Instruments for implementation

1. **The parental enhancing program**, developed by the researcher, is based on Belsky's "A Process Model of Competent Parental Functioning". The program consists of the following activities:

- Session 1 (24-48 hours postpartum): Establishes rapport and strengthens the mother-infant bond. The researcher provides personalized knowledge and skills training on recognizing infant cues and responsiveness, general infant care, breastfeeding techniques, bathing procedures, and identifying abnormal symptoms in infants, lasting about 60 to 90

minutes. Teaching materials, such as infographics, e-books, and instructional videos, are disseminated through the 'Line Official Account™ Parent Paplearn' as a mobile application.

- Session 2 (48-72 hours postpartum): Review the previously covered knowledge and offer additional skills training aimed at enhancing the mother's confidence. Individualized support is provided to address her specific concerns, lasting about 60 minutes.

- Session 3 (Post-discharge follow-up): Following discharge, the program includes weekly follow-up messages sent via mobile application through the 'Line Official Account™ Parent Paplearn' for five weeks to address any questions or concerns related to challenges faced by the mother or her infant.

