### **11.2 Data Collection**

1. The research proposal was submitted to the Ethics Committee of Queen Savang Vadhana Memorial Hospital, Thai Red Cross Society, to obtain permission for data collection.

2. Upon approval, the researcher submitted a formal request to the hospital director, which was forwarded to the Nursing Department and relevant ward supervisors to secure permission for data collection.

3. After receiving permission, the researcher introduced themselves to the ward supervisors, explained the study details, and requested cooperation in data collection.

4. The researcher collaborated with nurses to identify eligible participants who met inclusion criteria and obtained permission to meet them after 24 hours postpartum. During these meetings, the researcher explained the study objectives, procedures, and participants' rights. The nurses obtained consent from potential participants to allow the researcher to meet them. The sampling procedure for each group (Figure 3).

[figure not shown]

**Figure 3.** Flow diagram of study.

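### Groups are formed without randomisation, the researcher who helps recruit also teaches, and neither the described procedures nor the unadjusted t-test guards against selection

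*Protocol*

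**What the plan says.** Protocol section 9 gives the design in one sentence: "This study employed a quasi-experimental control group pre-post-test design". No section of the supplied text mentions randomisation, an allocation list or concealment. For the way each group is formed, section 11.2 item 4 points to a diagram that is not shown: "The sampling procedure for each group (Figure 3".

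On roles, section 11.2 says: "The researcher collaborated with nurses to identify eligible participants who met inclusion criteria and obtained permission to meet them after 24 hours postpartum". It adds: "The nurses obtained consent from potential participants to allow the researcher to meet them". Section 10.5 continues: "The researcher explained the study objectives, procedures, and participants' rights. Informed consent forms were then obtained from the participants". For the intervention, section 10.6.1 says: "The researcher provides personalized knowledge and skills training on recognizing infant cues and responsiveness". The same section has the researchers building and running the LINE account. The budget in section 19 also pays a research assistant, a postpartum nurse, whose tasks include sampling and data collection.

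Two inclusion criteria in section 10.4 call for judgement. One is "Mother intended to childcare for six-week"; the other is demonstrated ability to communicate through LINE.

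Both hypotheses in section 7 compare the groups, for example "Participants in the intervention group experienced significantly higher scores in parental competence compared to those in the control group". Section 12 item 4 tests them with an independent t-test and names no covariate. Item 2 compares the groups' characteristics by significance tests.

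**The concern.** In a non-randomised study, the groups can differ at entry in ways that affect the outcome. Mothers who are more motivated, better supported or more at ease with a phone may report less stress and more competence whatever the program does. If such mothers enter one group more often, even unintentionally, the difference appears in both outcomes and the t-test attributes it to the program. The shift could also run the other way and hide a real effect; the documents do not fix its direction.

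The risk is greater where a person with a role in recruitment also delivers the program and where eligibility rests partly on judgement. The result is also meant to be read as an effect: section 6 says the ongoing support relieves stress and improves competence.

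**Working it through.** **1. The plan's own sample size.** Section 10.3 gives a large effect, power 0.80, alpha 0.05 and 26 per group. Taking large as d = 0.8 and the test as two-sided (both assumptions, since neither is stated), the exact noncentral t calculation gives 25.52, rounded up to 26. Allowing for 10% dropout, 26 / 0.90 = 28.9, so 29; the protocol uses 30. The sample size is not in question, and randomising would not change it.

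**2. Effect of a selection shift on the planned test.** Let the program have no effect and the groups differ by b SD through selection. The t statistic then follows a noncentral t distribution with df = 2n − 2 and noncentrality b × √(n/2). The rejection rate is the probability that |t| exceeds the two-sided 5% critical value.

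For n = 30, √15 = 3.873 and df = 58, so b = 0.1 gives noncentrality 0.387 and b = 0.2 gives 0.775. For n = 26, √13 = 3.606 and df = 50.

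| Assumed shift b (SD) | n = 30 per group | n = 26 per group |
|---|---|---|
| 0 | 5.0% | 5.0% |
| 0.1 | 6.7% | 6.4% |
| 0.2 | 11.9% | 10.9% |
| 0.3 | 20.8% | 18.6% |
| 0.5 | 47.8% | 42.4% |

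If the shift favours the program, nearly all of the excess falls on that side. At n = 30, false positives in the program's favour go from 2.5% to 5.7% (b = 0.1) or 11.5% (b = 0.2).

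**3. Which shifts are plausible.** The documents give no value. As a scale, suppose the least engaged 10% of mothers were passed over in one group only. The mean of a standard normal with its lowest tenth removed is 0.195. With engagement perfectly correlated with the outcome, the shift is therefore 0.195 SD; at correlation 0.5 it is about 0.097 SD. This supports the rows 0.1 and 0.2. No mechanism has been worked out for 0.3 or 0.5; those rows only show how the rate grows.

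**4. Whether the baseline tests would reveal it.** At n = 30 a difference reaches significance only at an observed 0.52 SD. A baseline t-test on a continuous characteristic would flag a true 0.2 SD imbalance about 12% of the time, by the same calculation. A non-significant baseline table is little reassurance.

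**5. Overlap on the ward if groups run together.** Section 3 puts discharge at 2 to 3 days. Taking 3 days, 60 mothers occupy 180 mother-days. Data collection in section 18 runs from February to December 2023, 334 days: 180 / 334 = 0.54 enrolled mothers present on average. Over the assistant's six budgeted months (about 183 days), 180 / 183 = 0.98. With even enrolment, about one enrolled mother or fewer is present at a time.

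**The case against.** A reader might infer that the researcher personally puts mothers into groups, or that the next group is known at enrolment. The documents support neither. The procedure is in Figure 3, which is not shown and so cannot be called missing. Identification is shared with ward nurses, who make the first approach; section 10.5 puts the taking of consent in the passive; and sampling is among the research assistant's budgeted tasks. That the recruiter also teaches does stand.

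A reader might also take section 7 to contain causal wording that should be struck out. It does not: its hypotheses are comparisons. The effect wording is in section 6.

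A quasi-experimental design is openly declared and contradicts nothing else in the protocol. That is right: this is a weak design choice, not an inconsistency. The protocol is written largely in the past tense, with data collection scheduled to end in December 2023, so randomisation may come too late. That is why a fallback is needed.

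Measured safeguards exist. The questionnaire in section 10.6.2 records childcare support, income sufficiency, family structure and childcare experience, and there are pre-test scores. Selection visible in these could be adjusted for, but section 12 names no such adjustment. Adjustment also cannot reach what is not recorded: motivation is not measured, and self-esteem and the quality of the marital relationship, which the protocol's literature review lists as influences on competence, are not on the questionnaire.

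Finally, mothers in concurrent groups on one ward could show each other material. The risk is real but small, given the overlap computed above and the one-to-one teaching.

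**Conclusion.** The point holds in limited form. Allocation is non-random by the protocol's own label, the researcher who takes part in recruitment also teaches, the supplied text describes no protection against selection, and the planned t-test does not correct for it. A selection shift can therefore produce the difference that the hypotheses test.

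A cautious size is a rise in the false-positive rate from 5% to about 7% to 12% at 30 per group. It rests on an assumed shift of 0.1 to 0.2 SD, a two-sided 5% test and no program effect. It would be tempting to headline the 21% or 48% that go with 0.3 or 0.5 SD, but nothing in the documents supports shifts of that size. Confidence is medium, because Figure 3 might show a procedure that lessens the concern.

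**What to change.** Change section 9 to a randomised controlled pre-post-test design, and add to section 11.2:

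> After eligibility, signed consent and the pre-test PSI-4-SF and PSOC have been recorded, each mother is allocated 1:1 by opening the next sequentially numbered, opaque, sealed envelope. The list is computer-generated with varying block sizes and is prepared by an existing team member who neither recruits nor teaches. The link to the LINE account is given only after allocation.

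The cost is a protocol amendment, a list and 60 envelopes, with no additional participants, visits or staff. The downside is the small risk of shared material on one ward.

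If enrolment is already complete, compare the groups on the post-test score with adjustment for the pre-test score (analysis of covariance). Report the result as an association from non-randomised groups, and do not carry over section 6's wording that the program relieves stress or improves competence. This costs only a change to the analysis and the report, but it leaves selection on unmeasured traits in place.
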